### Sample size

PASS was used for sample size determination. According to the previous study [21] and clinical experience, the success rates of the EA, WA, MA, and SA groups are expected to be 70%, 65%, 60%, and 40%, respectively. A two-sided significance level of 0.05 will avoid the inflation of type I errors. A sample size of 45 patients in each group is estimated to have 80% power to detect significant differences between the groups. To compensate for a 10% loss in follow-up, the sample size was increased to 50 patients in each group.

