**Methods/design:**

A total of 200 eligible participants with KOA will be randomly assigned to group A, B, C, or D in a ratio of 1:1:1:1. Patients in group A will receive MA, while those in group B, group C, and group D will be treated with EA, WA, and sham acupuncture (SA), respectively. Patients will be treated with acupuncture once a day, 30 min per session, 5 sessions per week for 4 weeks. The primary outcome is the change of Western Ontario and McMaster Universities Osteoarthritis Index (WOMAC) at week 4. The secondary outcomes include WOMAC, visual analog scale (VAS), Arthritis Quality of Life Measurement Scale Simplified Scale (AIMS2-SF), Beck Anxiety Inventory (BAI), Beck Depression Inventory (BDI), and Credibility/Expectancy Questionnaire. The evaluation will be performed at baseline and weeks 4, 8, and 12 respectively after randomization.

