#### Primary outcome

We will use the Western Ontario and McMaster Universities Osteoarthritis Index (WOMAC) [22] as the primary outcome measure. The WOMAC is a valid and reliable self-administered questionnaire that has been used widely in a variety of clinical trials involving patients with KOA. It can be used as an initial assessment of the intensity of pain and functional disability of KOA. The Chinese version of WOMAC consists of 24 items assessing the patients with KOA pain (5 items), stiffness (2 items), and physical function (17 items). Therefore, it can multidimensionally measure pain, stiffness, and physical functional disability [23]. All 24 questions will be listed on a numerical rating scale ranging from 0 (no symptoms) to 4 (maximum symptoms). Doctors need to help patients perform the self-assessment, collect the total score from the 24 questions, and record it. Higher scores indicate more severe symptoms or physical disability. The evaluation will be performed at baseline and weeks 4, 8, and 12 respectively after randomization; then, we will select the evaluation at week 4 as the primary outcome.

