### Statistical analysis

Before the data analyses, the research group will provide a statistical scheme to the statisticians. The scheme will include the required data and processing method. The data will be processed and analyzed by the statisticians by the scheme.

Intention-to-treat statistical analysis will be conducted. Missing data will be treated by imputation methods depending on the type: missing completely at random, missing at random, or not at random. Per-protocol analysis will include only patients who attended at least 80% of the sessions and completed the follow-up in the allocated intervention group.

Statistical analyses will be performed with SPSS 22.0 statistics software (IBM Corporation, Armonk, NY, USA). The data analysis process will be completed by statisticians who are independent of the research team and blinded to the test settings. A *t*-test and Wilcoxon test will be used to compare the numerical variables in the within-group analyses, including the WOMAC, VAS, AIMS2-SF, BAI, and BDI. Analysis of variance and the Kruskal-Wallis test will be used for numerical variables in the between-group analyses, including age, height, weight, scores of VAS, WOMAC, AIMS2-SF, BAI, BDI, and Credibility/Expectancy Questionnaire. The chi-squared test and one-way analysis of variance (ANOVA) will be used for categorical variables such as the demographic and baseline characteristics. The available data of the four groups (group A, group B, group C, and group D) will be tested by bilateral tests and the confidence intervals are all 95% bilateral, with a *P* value less than 0.05 being statistically significant.

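### The sample size rests on undefined success rates, so the stated 80% power does not apply to the planned week-4 WOMAC analysis, whose power is not established

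*Protocol article*

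**What the plan says.** The Sample size section takes its inputs from a previous study and clinical experience: "the success rates of the EA, WA, MA, and SA groups are expected to be 70%, 65%, 60%, and 40%, respectively". It then states "A sample size of 45 patients in each group is estimated to have 80% power to detect significant differences between the groups", and for dropout "To compensate for a 10% loss in follow-up, the sample size was increased to 50 patients in each group". It names neither the test nor the comparison, and does not say what counts as a success.

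The abstract defines the endpoint differently: "The primary outcome is the change of Western Ontario and McMaster Universities Osteoarthritis Index (WOMAC) at week 4". The Primary outcome section describes a total over 24 items, each scored 0 to 4 (so 0 to 96), and says "we will select the evaluation at week 4 as the primary outcome". It gives no responder threshold. The secondary outcomes (WOMAC at weeks 8 and 12, VAS, AIMS2-SF, Credibility/Expectancy Questionnaire, BAI, BDI) are all scores as well.

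The Statistical analysis section says "Analysis of variance and the Kruskal-Wallis test will be used for numerical variables in the between-group analyses", and WOMAC is in the list that follows. The chi-squared test is mentioned for categorical variables, with demographic and baseline characteristics as the examples.

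**The concern.** A power statement holds for one endpoint, one test and one assumed effect. Here the assumed effect is a set of proportions, while the endpoint and the test are for a numerical score. No WOMAC difference and no WOMAC SD enter the calculation, so the 80% cannot be carried over to the primary analysis.

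What is at stake is the design rationale. The ethics committee, funder or reader is told that 80% power was planned, but not what WOMAC difference the trial is built to detect or whether that difference matters to patients. Since no test is named, it is also unclear whether the 80% refers to a global four-group test, to one active method against sham, or to comparisons among the active methods.

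**Working it through.** **Inputs from the protocol.** Rates 0.70 (EA), 0.65 (WA), 0.60 (MA), 0.40 (SA); two-sided alpha 0.05; power 80%; 45 evaluable per arm (180 in total); 10% dropout; 50 per arm (200 in total); 1:1:1:1 allocation.

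**1. Dropout step.** 45 / (1 − 0.10) = 50. This reproduces.

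**2. The plan's own figure, read as a four-group chi-square test (3 df).**
- Mean rate = (0.70 + 0.65 + 0.60 + 0.40) / 4 = 0.5875.
- Squared deviations: 0.01266, 0.00391, 0.00016, 0.03516. Their mean is 0.01297.
- w² = 0.01297 / (0.5875 × 0.4125) = 0.0535, so w = 0.231.
- Noncentrality = total N × w². At 45 per arm, 180 × 0.0535 = 9.63. Against the 3-df critical value of 7.81, power is 74.4% (74.8% by simulation).
- At 50 per arm power is 79.2%. The smallest size reaching 80% is 51 per arm.

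**3. The plan's own figure, read as a comparison of two proportions (two-sided 0.05).**

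| Comparison | n per arm for 80% | Power at 45 per arm |
|---|---|---|
| EA vs SA | 42 (49 with continuity correction) | 82.8% |
| WA vs SA | 62 | 66.6% |
| MA vs SA | 97 | 47.5% |
| EA vs MA | 356 | 16.6% |
| EA vs WA | 1377 | 7.3% |
| WA vs MA | 1471 | 7.1% |

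Pooling the three active arms against SA needs 41 in the SA arm (84.2% power at 45). The nearest of these to the stated 45 and 80% is EA vs SA, which misses by 3 patients and 2.8 percentage points. No two-sided 0.05 variant tried returns the stated pair.

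**4. The planned analysis: one-way ANOVA of week-4 WOMAC, four groups.** With f = SD of the group means / within-group SD, noncentrality is total N × f², with 3 and 176 df at 45 per arm.
- f = 0.25: 180 × 0.0625 = 11.25, power 80%.
- f = 0.10, 0.20, 0.30: power 17%, 59%, 93%.
- Smallest f for 80% power: about 0.25 at 45 per arm, about 0.24 at 50.

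What f = 0.25 means depends on the pattern of means. If the three active arms are equal and differ from sham by d SDs, then f = d × √(3/16) = 0.433d, so d = 0.25 / 0.433 = 0.58. If two arms are d apart and the other two lie midway, f = d × √(1/8) = 0.354d, so d = 0.25 / 0.354 = 0.71. The protocol gives no WOMAC SD. Under an assumed 12 to 20 points, the first pattern is about 7 to 12 points (0.58 × 12 = 7.0; 0.58 × 20 = 11.6) on the 0 to 96 scale.

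**5. If pairwise claims are intended.** Smallest difference with 80% power, two-sample t-test:

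| Alpha | 45 per arm | 50 per arm |
|---|---|---|
| 0.05 | 0.60 SD | 0.57 SD |
| 0.05/3 | 0.69 SD | 0.66 SD |
| 0.05/6 | 0.75 SD | 0.71 SD |

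**6. Which way could the error go?** Suppose, purely as an assumption, that success means passing a threshold on a normally distributed WOMAC change with equal SDs. The normal quantiles of 0.70, 0.65, 0.60 and 0.40 are 0.524, 0.385, 0.253 and −0.253. The shifts from sham are then 0.78, 0.64 and 0.51 SD, f is about 0.29, and ANOVA power is about 92% at 45 per arm (95% at 50).

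**The case against.** The strongest reply is that sizing on a dichotomised response is often conservative when the analysis keeps the score whole. Step 6 supports that: if success were a WOMAC threshold, the planned ANOVA would have more than the stated 80%. This stands as far as it goes. A reader might infer from the mismatch that the trial is underpowered, or that correcting the figure must make it less favourable. The documents support neither. They do not support the 92% either, because nothing in them ties success to WOMAC.

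A reader might also infer that a null primary result could not be interpreted. That goes too far. The Statistical analysis section commits to two-sided 95% confidence intervals, and a null result can be read from those. A faulty planning figure biases neither the estimate nor the type I error of the WOMAC test.

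Finally, this is a condensed article. The definition of success may sit in the full protocol or in the cited previous study, and the chi-squared test is not strictly confined to baseline variables. That tempers any claim that success is defined nowhere. It does not remove the conflict, because the article itself gives a sample-size basis in one metric and a primary outcome and between-group test in another.

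**Conclusion.** The point holds in this form: the 80% power does not belong to the primary analysis, and power for that analysis is not established. Whether it is above or below 80% cannot be determined from the protocol, since no WOMAC difference or SD is given. What can be said is that 45 per arm reaches 80% for the planned ANOVA only when f is about 0.25 or more.

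Separately, the stated figure does not reproduce on its own inputs if the test is the four-group chi-square: 74.4% rather than 80% at 45 per arm, and 51 rather than 45 per arm needed. That conclusion depends on the test, which the protocol does not name. EA against SA alone would have slightly more than 80%.

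The ANOVA figures assume normal scores, a common SD and equal arms of 45 or 50. The conversion to points rests on an assumed SD of 12 to 20.

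**What to change.** Keep 50 per arm and replace the success-rate basis with a statement for the planned analysis, for example: *With 45 evaluable patients per arm, the four-group ANOVA of week-4 WOMAC has 80% power at two-sided 0.05 for a Cohen f of about 0.25 (about 0.24 at 50 per arm).* Translate this into WOMAC points with an explicitly assumed and sourced SD, and say why a difference of that size is plausible and worth detecting. A detectable effect alone describes the sample size but does not justify it.

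If pairwise claims are intended, name the comparisons and the alpha for each, and add the detectable differences at 45 per arm: about 0.60 SD for one comparison, 0.69 SD at 0.05/3, 0.75 SD at 0.05/6.

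The alternative is to keep the rates, define success on WOMAC, state its analysis and its relation to the primary outcome, name the test, and correct the power (74.4% at 45 per arm for the four-group chi-square).

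The first route costs one paragraph of wording, with no change to the number of patients, the endpoint or the planned test. The alternative also adds an outcome definition and its analysis.

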## Methods and analysis

### Study design

This is a randomized controlled trial (RCT) that aims to compare the effect of MA, EA, and WA acupuncture methods in the treatment of KOA. This trial has been approved by the ethical committees of the First Affiliated Hospital of Henan University of Traditional Chinese Medicine (No: 2021HL-158) and registered in the Chinese Clinical Trial Registry, ChiCTR2100049526. The protocol will be reported following Standard Protocol Items: Recommendations for Interventional Trials (SPIRIT) reporting guidelines [18] (Additional file 1). A total of 200 patients diagnosed with KOA according to the American College of Rheumatology clinical criteria will be recruited [19]. After informed consent acquisition, all patients will be randomly assigned to group A (MA group), group B (EA group), group C (WA group), and group D (SA group) based on the ratio of 1:1:1:1, to receive treatment. The treatment procedure will include 20 sessions of treatments in total from baseline to week 4 and 2 times of follow-ups on week 8 and week 12 respectively. Outcome measurements will be assessed according to the following time schedule. Figure 1 shows the study design in the flowchart, and Table 1 illustrates the time schedule of enrolment, interventions, assessments, and visits of participants.

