### Randomization

In this trial, eligible patients who consent to participate will be randomly assigned to one of four groups via a central randomization system for clinical research in a ratio of 1:1:1:1 by an independent researcher, who will not be involved in the implementation or statistical analysis of the trial. Random number lists will be created by PROCPLAN of SAS 9.2 (SAS Institute Inc., Cary, NC, USA). The randomization allocation will use sequentially numbered, opaque, and sealed envelopes. The participants’ screening sequence numbers will be printed outside the envelope, whereas the group names will be printed inside. After a participant has met all selection criteria, signed the informed consent form, and completed the baseline assessments, the researcher will inform the statisticians in the center. The statisticians will open the envelope according to the participant’s screening sequence number and then assign the participant to one of the four groups.

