
We will analyze and compare the therapeutic effects of MA, EA, WA, and SA, which will provide not only evidence for different kinds of acupuncture treatments to relieve pain and improve physical function in KOA patients but also visualization reference for the clinical application of acupuncture for KOA management.

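### The sample-size section says a two-sided 0.05 level avoids type I error inflation; it controls a single test, not the pairwise comparisons the trial aims to make

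*Protocol article*

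**What the plan says.** The protocol article randomises patients to four arms: manual (MA), electro- (EA), warm (WA) and sham acupuncture (SA). They are "randomly assigned to one of four groups via a central randomization system for clinical research in a ratio of 1:1:1:1".

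Study design gives the purpose: the trial "aims to compare the effect of MA, EA, and WA acupuncture methods in the treatment of KOA". The closing paragraph of the Discussion, under Strict quality control, adds sham: "We will analyze and compare the therapeutic effects of MA, EA, WA, and SA".

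On error control, Sample size says: "A two-sided significance level of 0.05 will avoid the inflation of type I errors". The same paragraph says that "the success rates of the EA, WA, MA, and SA groups are expected to be 70%, 65%, 60%, and 40%, respectively", and then: "A sample size of 45 patients in each group is estimated to have 80% power to detect significant differences between the groups".

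Statistical analysis names analysis of variance and the Kruskal-Wallis test for between-group comparison of scores. It adds that the data of the four groups "will be tested by bilateral tests and the confidence intervals are all 95% bilateral", with P below 0.05 as the threshold. It names no pairwise test. The primary outcome is WOMAC at week 4.

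**The concern.** The statement in Sample size treats the choice of a per-test level as if it dealt with multiplicity. In a four-arm trial, inflation arises from making several comparisons, and a 0.05 level for each does nothing about that.

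The sentence matters because of the trial's aim. To say that one method outperforms another, or outperforms sham, takes pairwise contrasts. An omnibus test shows only that the four arms are not all alike. An analyst who relies on the sentence has reason to think that no adjustment is needed for those contrasts, and a reader has reason to think that a claimed superiority carries a 5% error rate.

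**Working it through.** **Inputs.** Four equal arms (Randomization); two-sided 0.05, 80% power, 45 per group, and success rates of 70% EA, 65% WA, 60% MA, 40% SA (Sample size). The number of pairs among four arms is 4×3/2 = 6. This is arithmetic; the protocol does not list six comparisons.

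**1. The plan's own figures.** The dropout step reproduces: 45/(1 − 0.10) = 50. The 80% power at 45 per group does not match any one comparison tried. A 3-df chi-squared test on the four rates has 74.4% power at 45 and needs 51 per group. EA versus SA has 82.8% and needs 42. The comparison meant is not named, which matters for the cost in step 5.

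**2. Pairwise tests at 0.05, unadjusted, no true differences.** With equal arms, at least one |z| exceeds 1.96 exactly when the studentized range exceeds 1.96×√2 = 2.77.

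| Family | Chance of at least one false positive |
|---|---|
| All six pairs (range of 4) | 20.3% |
| MA, EA, WA among themselves (range of 3) | 12.2% |
| Three active versus sham (simulation) | 12.5% |

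For six independent tests the figure would be 1 − 0.95⁶ = 26.5%. It is lower here because pairs share arms.

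**3. Omnibus test as a gate.** The simulation used 45 per arm, normal data with common variance, an F test at 0.05, and pairwise t-tests at 0.05 only if F is significant. MA, EA and WA are equal; only sham is moved.

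| Sham apart by | Omnibus rejects | False claim among MA, EA, WA |
|---|---|---|
| 0.4 SD | 46% | 9.9% |
| 0.6 SD | 84% | 11.9% |
| 1.0 SD | over 99% | 12.1% |

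With all four arms equal the gate holds 5.0% over all pairs. Once sham differs, it opens because of sham and gives the active-versus-active comparisons little protection.

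**4. Is 0.4 to 1 SD a fair range?** The protocol gives no WOMAC difference or SD, so this is an assumption. If success were a cut-off on a normal score with common SD, 60% versus 40% would correspond to 0.253 + 0.253 = 0.51 SD, and 70% versus 40% to 0.524 + 0.253 = 0.78 SD. Both lie inside the range.

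**5. Power cost of adjustment, on the protocol's rates at 45 per group.** Power = Φ[(d − z·se₀)/se₁], with se₀ from the pooled and se₁ from the separate variances. For EA versus SA: d = 0.30, se₀ = √(2×0.55×0.45/45) = 0.1049, se₁ = √((0.21 + 0.24)/45) = 0.100.
- At 0.05: z = 1.960, Φ(0.944) = 83%.
- At 0.05/6 = 0.0083: z = 2.638, Φ(0.233) = 59%.

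| Pair | 0.05 | Bonferroni over 6 | Bonferroni over 3 |
|---|---|---|---|
| EA-SA | 83% | 59% | 69% |
| WA-SA | 67% | 39% | 49% |
| MA-SA | 47% | 22% | 31% |

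Active-versus-active power is 7% to 17% unadjusted and 2% to 5% with Bonferroni over six.

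**The case against.** The strongest reply is that the only between-group tests named are four-group omnibus tests, and that there is one primary measure at one time. A single omnibus test of week-4 WOMAC at 0.05 does hold 5%. That stands, and for that one test the sentence does no harm.

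A reader might infer that the protocol plans six pairwise comparisons, each judged at an unadjusted 0.05. The document does not support this. It never lists six comparisons and names no pairwise test. Its P<0.05 threshold does not exclude adjustment, because Tukey- or Holm-adjusted P values are also compared with 0.05. Statistical analysis also says that a scheme with the processing methods will go to the statisticians before analysis. That scheme is not shown, and post-hoc procedures may well be in it. The absence of an adjustment method from the article is therefore not the finding, and the percentages above are conditional on unadjusted pairwise testing.

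This reply does not rescue the sentence itself. A later scheme could override it but cannot make it true, and the stated aim goes beyond what an omnibus test can answer.

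It is also fair to say that the choice of family is partly preference. All six pairs, the three against sham, or an ordered sequence can each be defended.

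**Conclusion.** The concern holds in a limited form. The sentence in Sample size credits the 0.05 level with a protection it does not give for the pairwise comparisons that the aim requires. If those comparisons were run unadjusted with no true differences, family-wise error would be 20.3% for six pairs and about 12.5% for three against sham. An omnibus gate restores 5% only when all four arms are equal. It leaves about 10-12% among equal active arms when sham is 0.4 to 1 SD away, close to what the protocol's success rates suggest.

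These figures assume equal arms, a common variance, approximately normal data and an unadjusted pairwise analysis that the protocol neither specifies nor excludes. The point should be fixed. It is not a fatal flaw, because the omnibus test of the primary outcome is sound at 5% and the remedy can be stated before analysis.

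**What to change.** - Delete the sentence on avoiding inflation from Sample size.
- Name the confirmatory pairwise comparisons of week-4 WOMAC: all six, or a smaller or ordered family such as active versus sham first.
- Control their family-wise two-sided error at 0.05 with Tukey, Holm or a stated gate. Do not rely on a significant four-group omnibus test for protection.
- State which comparison the 80% power refers to, and give its power at the level at which it will be tested.

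No new data or visits are needed, but the change is more than wording because power per comparison falls. The Bonferroni figures in the working are the conservative end; Holm or a smaller family loses less. Since 45 per group gives well under 80% for most pairs even unadjusted, naming the family will expose the sample-size claim to re-examination.

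### The stated 80% power at 45 per group does not follow from the assumed success rates: the four-group test has about 74%, and only EA versus sham exceeds 80%

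*Protocol article*

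**What the plan says.** The Sample size section gives all the inputs of a calculation on proportions. It states that "the success rates of the EA, WA, MA, and SA groups are expected to be 70%, 65%, 60%, and 40%, respectively", fixes a two-sided 0.05 level, and concludes: "A sample size of 45 patients in each group is estimated to have 80% power to detect significant differences between the groups". The number is then raised for attrition: "To compensate for a 10% loss in follow-up, the sample size was increased to 50 patients in each group". The section does not name the test or the contrast to which the 80% applies.

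The Study design section says the trial "aims to compare the effect of MA, EA, and WA acupuncture methods in the treatment of KOA". The closing paragraph of the Discussion, under Strict quality control, widens this: "We will analyze and compare the therapeutic effects of MA, EA, WA, and SA".

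The Primary outcome section makes the week-4 WOMAC score the primary outcome. The Statistical analysis section compares it between groups by analysis of variance or Kruskal-Wallis. The article does not define what counts as a success.

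**The concern.** The plain reading of the power statement is a test across all four groups. A reader could also take it to cover the comparisons for which the trial is run. On the section's own rates neither reading gives 80%.

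The gap is widest for the comparisons in the stated aim. The three active arms are assumed to differ by only 5 to 10 percentage points, and 45 per group cannot reliably detect that. Under these assumptions a true difference between two active arms would be missed about 83–92% of the time. A reader who believes the power is 80% would take such a null result as informative. The abstract says the trial is meant to lead to standardised treatment programmes, so that misreading could matter.

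**Working it through.** **Inputs** (Sample size section, except the ratio): success rates 0.70, 0.65, 0.60 and 0.40; two-sided α = 0.05; 45 evaluable per group, 180 in total; 10% loss; allocation 1:1:1:1 (abstract). Assumption: since the test is not named, the Pearson chi-square is used.

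**Attrition step.** 45 / 0.9 = 50 per group, 200 in total. This reproduces.

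**Four-group test, 3 degrees of freedom.** Noncentrality λ = n Σ(pᵢ − p̄)² / [p̄(1 − p̄)].
- p̄ = (0.70 + 0.65 + 0.60 + 0.40) / 4 = 0.5875, so p̄(1 − p̄) = 0.24234.
- Σ(pᵢ − p̄)² = 0.1125² + 0.0625² + 0.0125² + 0.1875² = 0.051875.
- λ = 45 × 0.051875 / 0.24234 = 9.63.
- Power from the noncentral chi-square = **74.4%**.

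Other versions at 45 per group agree: likelihood ratio 74.2%, arcsine 74.6%, simulation 74.8%, ANOVA on the 0/1 outcome 75.9%. The stated 80% is not reproduced. With the chi-square, 50 per group gives 79.2% and 51 gives 80.1%.

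**Pairwise contrasts, two-sided 0.05, unadjusted.** With d = |p₁ − p₂| and p̄ the mean of the two rates:
- s₀ = √[2p̄(1 − p̄)/n] and s₁ = √{[p₁(1 − p₁) + p₂(1 − p₂)]/n}
- power = Φ[(d − 1.96 s₀)/s₁] + Φ[(−d − 1.96 s₀)/s₁]

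Example, EA versus SA: d = 0.30; s₀ = √(2 × 0.55 × 0.45/45) = 0.1049; s₁ = √[(0.21 + 0.24)/45] = 0.100. The first term is Φ[(0.30 − 0.2056)/0.100] = Φ(0.944) = 0.828, and the second is negligible.

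| Contrast | Rates | Power at 45 per group | n per group for 80% |
|---|---|---|---|
| EA vs SA | 70% vs 40% | 82.8% | 42 |
| WA vs SA | 65% vs 40% | 66.6% | 62 |
| MA vs SA | 60% vs 40% | 47.5% | 97 |
| EA vs MA | 70% vs 60% | 16.7% | 356 |
| EA vs WA | 70% vs 65% | 8.0% | 1377 |
| WA vs MA | 65% vs 60% | 7.8% | 1471 |

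The last column is before any allowance for loss.

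**Is there a reading that gives 80% at 45?** EA versus SA comes closest: 82.8% by the formula above and 81.8% by exact enumeration of the uncorrected chi-square. It does not return 45 as the required number, though. The pooled formula gives 42 and the continuity-corrected one 49. Fisher's exact test has 75.8% at 45, and a Bonferroni correction for three comparisons gives 68.8%. An ordered trend test would have 82.5%, but none is planned. A one-sided unpooled test of WA versus SA would have 79.0%, but the article specifies two-sided testing.

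**The case against.** Four points can be made for the plan.

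- **EA versus SA reaches about 80%.** True, unadjusted, and the write-up should say so. It would be too strong to infer that no reading supports the figure. But the sentence follows a list of four rates and speaks of the groups in general. Nothing restricts it to the largest contrast.
- **The four-group shortfall is modest.** Also true: about 6 points, or 51 against 45 evaluable per group. Intention-to-treat with imputation nominally analyses 50 per group, for 79.2%. That is an upper bound, because imputation does not restore lost information, and the section attaches the 80% to 45.
- **The figures concern an endpoint that the trial does not name as an outcome.** This stands and limits the point. A reader might infer that the primary analysis is underpowered. The article does not support that: it gives no WOMAC mean difference or standard deviation, so that power is unknown in either direction.
- **No equivalence conclusion is planned.** Correct. A reader might infer that the trial intends to declare the three methods equal if they do not differ significantly, but nothing in the article says so. The risk is one of later misreading, which a sentence can prevent.

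The Statistical analysis section already specifies two-sided 95% confidence intervals, so that part of the fix mainly directs existing practice to the active-versus-active contrasts.

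**Conclusion.** The 80% statement is wrong as written. Under the assumed success rates, 45 per group gives about 74% for the four-group chi-square. Unadjusted pairwise power is about 83% for EA versus SA, 67% for WA versus SA, 47% for MA versus SA and 8–17% between active arms. The attrition step is correct.

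This rests on the article's rates and two-sided 0.05 level, and on a chi-square or two-proportion test, because the section names none. The four-group result varies by less than 2 points across the standard versions tried. It is a finding about the success-rate calculation and says nothing of the power of the week-4 WOMAC analysis.

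**What to change.** Replace the power sentence in the Sample size section, with no change to enrolment. Suggested content:

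> For the assumed success rates (70%, 65%, 60%, 40%) and 45 evaluable patients per group at a two-sided 0.05 level, power is about 74% for a four-group chi-square test. Without adjustment for multiple comparisons it is about 83%, 67% and 47% for EA, WA and MA versus SA, and 8–17% for comparisons between active arms. These figures refer to the assumed success rates; power for the primary week-4 WOMAC comparison was not derived from them. Contrasts between active arms will be reported as estimates with 95% confidence intervals, and a non-significant result will not be read as equal efficacy.

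If the 80% was meant for one contrast, the alternative is to name it (EA versus SA, unadjusted) and keep the last two sentences. If it came from another calculation, the sponsor should state the endpoint, test and contrast used.

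The cost is protocol wording only. The downside is that the stated power becomes less favourable.
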